### Quantitative data

This feasibility trial will explore the most appropriate primary outcome for a fully powered RCT. Data analysis, following intention-to-treat principles, will focus on descriptive statistics and feasibility outcomes, consistent with the primary aims and objectives of the trial. Summaries, including completeness, for outcome measures and important demographic covariates will be reported by group. No missing data will be imputed. While clinical effectiveness will not be definitively assessed at this stage, we will explore hypotheses that measures of depression, anxiety and stress (as operationalised by the DASS) will diminish, and measures of PERMA and HRV will improve, using a split-plot ANOVA with group (intervention vs control) as a between-subjects factor across time (pre vs two follow-up assessments), a within-subject factor. All assessments will be summarised using two-sided tests and 95% confidence intervals where appropriate. Estimates of treatment effect size and intraclass correlations will be used to inform sample size considerations for a full-scale RCT.

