**Methods and analysis:**

A randomised, two-arm feasibility trial involving allocation of patients to either a treatment group (positive psychotherapy) or control group (treatment as usual) group, according to a 1:1 ratio. A total of 60 participants at three sites will be recruited including 20 participants at each site. Assessments will be conducted at baseline, on completion of the 8-week intervention and 3 months following completion. These will include a range of questionnaire-based measures, psychophysiology and qualitative outcomes focusing on feasibility outcomes and participant experience. This study has been approved by the Wales Research Ethics Committee (IRAS project ID: 271,251, REC reference: 19/WA/0336).

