### Participants

Participants (*N* = 60) and mentors (*N* = 6) with a confirmed diagnosis of ABI will be recruited across three participating local health board sites: Swansea Bay University Health Board (SBUHB), Hywel Dda University Health Board (HDUHB) and Cardiff and Vale University Health Board (CVUHB). Sample size was determined based on our clinical experience running similar interventions, which typically involve 10 participants and 2 mentors per group and 2 courses per year. Quantitative analysis on collected data will provide us with more guidance on which sample size calculation for a full-scale RCT will be based.

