### Design

The study will randomly allocate eligible patients to either the treatment (positive psychotherapy [PP] intervention) or control (TAU) at a 1:1 ratio with stratification by site and antidepressant use (yes/no) (see further details below under ‘Randomisation’). The choice of a TAU control condition was based on ethical considerations and also enabled comparisons with past research [10, 11, 13]. Data collection will take place at each of the three healthcare sites, capturing a diverse representation of patients and enhancing the generalizability of the findings beyond a single site.

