### Randomisation

Participants will be randomly allocated to the intervention or TAU using REDCap [22, 23]. An authorised person will access REDCap to determine allocated treatment once eligibility has been confirmed. The participant will be notified of the allocation and the days on which the intervention will be delivered (if randomised to the intervention arm). The randomisation algorithm will be designed to promote balance in the sample sizes of the intervention and control groups, although exact numbers may vary slightly due to stratification for site (i.e. 3 sites; aiming for 10 participants per site, per arm) and antidepressant use (i.e. yes/no; aiming for an equivalent number of participants prescribed antidepressants per site, per arm).

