### Procedure

The study will involve the following key stages (see also Fig. 1, Table 2):*Referral*: Potential participants and mentors will be asked whether they would like to participate in the study and will be given the participant or mentor information sheet as appropriate.*Consent*: Potential participants and mentors meet a member of the research team to discuss the study and provide consent.*Eligibility*: Potential participants and mentors meet with the research assistant (under the supervision of a clinical psychologist) to determine eligibility for the study. If participants are deemed ineligible, they will be followed up by the PI and an explanation given.*Baseline measures*: Eligible participants and mentors meet with the research assistant to complete baseline measures. A detailed description of the measures are provided below.*Randomisation*: Participants will be randomly assigned to the TAU control group or the PP intervention group. Two mentors will be assigned to each of the three intervention groups based on availability and proximity.*Treatment*: Participants and mentors attend the 8-week PP group or TAU control.*Immediate follow-up*: All participants meet the research assistant to repeat quantitative measures over a 2-week period following the final session of the 8-week-positive psychotherapy intervention. Group attendees and mentors will also be invited to take part in participant and mentor focus groups, respectively, to gather data for qualitative analysis.*Three-month follow-up*: All participants meet the research assistant to repeat quantitative measures a final time, 3 months following the final session for the intervention.

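### The exploratory split-plot ANOVA assumes independent participants although positive psychotherapy is delivered in three groups; with any positive therapy-group correlation its intervals are too narrow and its p-values too small

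*Protocol article*

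**What the plan says.** Under Quantitative data, the protocol article explores whether depression, anxiety and stress scores fall and whether PERMA and heart rate variability improve, "using a split-plot ANOVA with group (intervention vs control) as a between-subjects factor across time (pre vs two follow-up assessments), a within-subject factor". Arm and time are the only factors named. It adds: "All assessments will be summarised using two-sided tests and 95% confidence intervals where appropriate". Intraclass correlations appear in that section only as an input to the sample size of the later full-scale trial.

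The delivery format is described elsewhere:
- Participants describes past courses, "which typically involve 10 participants and 2 mentors per group and 2 courses per year".
- Randomisation allocates individuals, stratified by site and antidepressant use, "aiming for 10 participants per site, per arm".
- Procedure states: "Two mentors will be assigned to each of the three intervention groups based on availability and proximity".

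So about 30 PP participants sit in three therapy groups of about 10. TAU has no fixed cohort. It is tailored to the person and may be individual or group care (Treatment as usual).

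**The concern.** Members of one PP group share mentors, sessions and each other's company. Their follow-up scores may therefore share a component that varies from group to group. The ANOVA error terms contain only variation between and within individuals, so the reference distribution in effect sets that shared component to zero. A significant arm-by-time result could then reflect one or two groups that happened to go well or badly, rather than an average effect over groups that might be run.

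Individual randomisation does not remove this, because the component arises after randomisation and only in PP. Nor does stratifying by site: a stable site difference common to both arms cancels from the arm-by-time contrast.

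At stake is how much confidence to place in any early signal on the DASS, PERMA or heart rate variability. The article accepts for the next trial that clustering matters, but its own intervals do not allow for it.

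**Working it through.** **Planned number.** 3 sites × 2 arms × 10 = 60, which agrees with the article: "A total of 60 participants at three sites will be recruited including 20 participants at each site". There is no power calculation to reproduce.

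**Inputs from the article.** Three PP groups of m = 10; TAU n = 30; three visits; two-sided tests and 95% intervals, so a nominal 5% level is implied.

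**Inputs assumed.** Raw-score therapy-group ICC of 0, 0.02, 0.05 or 0.10; visit correlation r of 0.5 to 0.8; person-plus-error variance 1 at each visit; a group component of variance τ² = ICC/(1 − ICC), present in PP only, at both follow-ups and with the same value at each; TAU participants independent; no average PP effect.

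**Standard error of the PP-minus-TAU difference in change from baseline.** The change-score variance within a group is 2(1 − r).
- True variance: 2 × 2(1 − r)/30 + τ²/3.
- Variance from the observed within-arm spread, ignoring groups: [4(1 − r) + τ² × 20/29]/30.

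At ICC 0.05 and r = 0.7, τ² = 0.0526. The true SE is √(0.0400 + 0.0175) = 0.240. The SE ignoring groups is √[(1.2 + 0.0363)/30] = 0.203. The ratio is 1.18. Across r = 0.5 to 0.8 the ratio is:
- ICC 0.02: 1.05 to 1.11
- ICC 0.05: 1.11 to 1.26
- ICC 0.10: 1.22 to 1.48

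**Type I error of the arm-by-time F test.** 20,000 simulated null trials per setting, ranges over r = 0.5 to 0.8:

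| Assumed raw-score ICC | 10 analysed per group | 7 analysed per group |
|---|---|---|
| 0 | 5% | 5% |
| 0.02 | about 6–8% | about 6–7% |
| 0.05 | about 7–12% | about 7–9% |
| 0.10 | about 10–18% | about 9–14% |

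The 7-per-group column allows for 30% missing data; the article imputes nothing. Repeat runs differ by up to about half a percentage point. With 10 per group, coverage of the nominal 95% interval is about 92–88% at ICC 0.05 and 89–82% at ICC 0.10.

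**What the upper ends mean.** The ICC on the change score is τ²/[2(1 − r) + τ²]. At r = 0.5 it equals the raw-score label. At r = 0.8 it is 0.0526/0.4526 = 0.12 for raw ICC 0.05, and 0.1111/0.5111 = 0.22 for raw ICC 0.10. The highest error rates therefore belong to change-score ICCs about twice the label.

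**Site differences.** Adding stable site effects common to both arms (site ICC 0.05 or 0.10, r = 0.6) leaves the arm-by-time error at about 8% for therapy-group ICC 0.05 and 12% for 0.10.

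**The case against.** The strongest reply is that nothing decisive rests on these tests. The primary endpoints are the feasibility criteria in Table 3, and none uses DASS, PERMA or heart rate variability. The article says effectiveness is not definitively assessed and that the analysis centres on description. This stands, and it is why the point is modest.

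A reader might infer that these p-values and intervals are the declared source of what passes to the full trial. The article does not say so. Objectives attributes early indications to the whole dataset, including qualitative and economic data, and Quantitative data passes on effect-size estimates and intraclass correlations. Ignoring clustering does not bias the estimated difference in this balanced design.

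The size is also assumed. At an ICC near 0.01 the effect is negligible (error about 5.6%, r = 0.6), and missing data shrink it. Nor does the article state that each group has a different facilitator; the mentors are what it makes group-specific. TAU may include group care, so independence in TAU is an assumption too.

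Finally, inference conditional on the three groups delivered is defensible in a feasibility study, especially as the group effect cannot be separated from a site-by-arm effect if there is one group per site. But the article does not label its intervals that way. Exploratory status lowers the stakes without making the stated coverage right.

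**Conclusion.** The point holds, conditionally. The named model does not match the stated delivery format, and its intervals are too narrow and its p-values too small if the therapy-group ICC is positive. Under the assumptions above the distortion is slight at ICC 0.02. It becomes material from about 0.05 and at 0.10 reaches two to three and a half times the nominal 5% with 10 per group. It would be wrong to say that the intervals are certainly too narrow, that the effect estimates are biased, or that the decision to progress is compromised: the documents give no ICC, and the progression criteria do not use this comparison. What is affected is the stated precision of an exploratory comparison. That deserves correction, but it is no threat to the trial's primary purpose.

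**What to change.** In Quantitative data:
1. Label the ANOVA tests and intervals as conditional on the three PP groups delivered.
2. For each key PP-minus-TAU difference in change from baseline, add 95% intervals under fixed assumed therapy-group ICCs, for example 0.02, 0.05 and 0.10. Three groups cannot supply a usable variance estimate, so the ICC should be fixed rather than fitted.
3. Use variance = s²_TAU/n_TAU + s²_PP/n_PP + τ²/3. Here s² is the within-arm variance of the change score (within therapy group for PP) and τ² = ICC × the outcome variance at that visit. With unequal groups, replace 1/3 by the sum of squared group shares, Σ(n_g/n_PP)².
4. State the reference distribution. A t distribution with n_TAU + n_PP − 2 degrees of freedom gave about 95% coverage in simulation when the assumed ICC was the true one.
5. State that clustering from any TAU group care is assumed to be nil.
6. Use these intervals, not the plain ANOVA p-value, when describing early indications of impact.

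The cost is wording and extra output: three more intervals per key outcome and visit, with no new data or patients. With 10 per group, intervals become about a tenth to a quarter wider at ICC 0.05 and about a fifth to just under a half wider at ICC 0.10. The results also then rest on an assumed ICC range.

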Intervention adherence (%) — participants	Attendance at a minimum of six sessions will be used to measure adherence. Full or partial completion of the two pieces of mandatory homework allocated to participants during session 1 and session 5 will also be documented. Setting the threshold at 75% ensures that participants are engaging in at least six of eight sessions of the intervention while also mindful of potential challenges participants may face such as scheduling conflicts and unexpected circumstances	< 75%	≥ 75%
Data collection	Success would be indicated if completion rates for post-intervention assessment and follow-up data collection reach a satisfactory threshold, taking into account practical considerations including participant compliance and capacity, versus representativeness and generalisability. Missing data will be reported	< 70%	≥ 70%
Attrition rates	Attrition will be calculated as the percentage of participants dropping out of the study relative to the numbers recruited. Reasons for withdrawal and loss to follow-up will be reported. Setting an attrition threshold at 40% acknowledges the potential challenges of participant retention in longitudinal studies	≥ 40%	< 40%

In the event that any of the feasibility criterion fail to meet the established targets for progression (Table 3), a comprehensive assessment will be undertaken that explores the reasons for the failure and determines the appropriate course of action. Based on that assessment as well as more general considerations relating to the detailed acceptance checklist [19], the research team will consider available options to address the feasibility challenges with the aim of optimising recruitment strategies and trial design. Ultimately, the decision to progress to a full-scale randomized controlled trial (RCT) will be based on a careful evaluation of the feasibility challenges in relation to the team’s capacity to run a future trial with confidence and achieve its objectives. The aim will be to strike a balance between addressing the identified challenges and ensuring the feasibility and success of the full-scale RCT. This approach will enhance the team’s ability to gather robust data, meet scientific standards and ultimately contribute valuable insights to the field of study.

These feasibility data will be complemented by inspection of additional quantitative, qualitative, psychophysiological and health economic data, as outlined in further detail below.

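### The exploratory split-plot ANOVA without imputation is in effect a complete-case analysis, which conflicts with the stated intention-to-treat principle; a mixed model using all available data would resolve this

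*Protocol article*

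**What the plan says.** One paragraph of the protocol article, Quantitative data, sets three things together.

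- The principle: "Data analysis, following intention-to-treat principles, will focus on descriptive statistics and feasibility outcomes".
- The missing-data rule: "No missing data will be imputed".
- The model for DASS, PERMA and HRV: "using a split-plot ANOVA with group (intervention vs control) as a between-subjects factor across time (pre vs two follow-up assessments), a within-subject factor".

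The paragraph marks this model as exploratory: "While clinical effectiveness will not be definitively assessed at this stage, we will explore hypotheses". It also says that effect sizes and intraclass correlations will inform the sample size of the full trial, and that completeness will be summarised by group. It does not say how a participant with one missed visit enters the ANOVA.

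Table 3 (Analysis) shows what losses the protocol would tolerate. Data collection passes at 70% completion or more. Attrition passes below 40%: "Setting an attrition threshold at 40% acknowledges the potential challenges of participant retention in longitudinal studies". Table 3 does not say whether the 70% applies per visit, pooled over visits, or to both visits jointly.

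**The concern.** A split-plot ANOVA in its usual least-squares form works on complete rows: baseline, immediate follow-up and 3-month follow-up. With imputation ruled out, a participant who attends at 8 weeks but not at 3 months is removed altogether, and the observed 8-week outcome goes unused. No method can recover outcomes that were never measured. Discarding measured outcomes from randomised participants is a separate matter, and it does not fit an intention-to-treat label.

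Two things are at stake. The first is precision in an already small sample. The second is bias: if those who leave after the 8-week visit differ in their 8-week scores, and differ by arm, the 8-week contrast among completers is distorted. Both carry over into the estimates meant for planning the full trial.

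**Working it through.** **Sample size.** The Abstract says: "A total of 60 participants at three sites will be recruited including 20 participants at each site". Randomisation gives the breakdown: "3 sites; aiming for 10 participants per site, per arm". So 3 × 2 × 10 = 60, which agrees. There is no power calculation to reproduce (Participants: "Sample size was determined based on our clinical experience running similar interventions"), and no expected dropout or complete-case number is stated.

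**Complete cases.** Let c be the completion rate at each of the two follow-ups, with baseline complete. The complete-case fraction is 2c − 1 if nobody misses both visits, c² if missingness is independent between visits, and c if the same people miss both.

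| c per visit | No overlap | Independent | Same people miss both |
|---|---|---|---|
| 70% (Table 3 pass floor) | 60 × 0.40 = 24 | 60 × 0.49 = 29 | 60 × 0.70 = 42 |
| 80% (assumed) | 60 × 0.60 = 36 | 60 × 0.64 = 38 | 60 × 0.80 = 48 |
| 90% (assumed) | 60 × 0.80 = 48 | 60 × 0.81 = 49 | 60 × 0.90 = 54 |

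If the 70% is pooled over both visits (84 of 120 assessments), the bounds are the same: at least 84 − 60 = 24 and at most 84/2 = 42. If it applies to both visits jointly, at least 42 remain. The largest attrition that passes is 23/60 = 38.3%, which leaves 37.

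**What a model for partial records would use at 70% per visit.** It uses everyone with at least one follow-up: 60 × (1 − 0.3²) = about 55 if independent, against 29 complete cases; 60 against 24 with no overlap; 42 against 42 if the same people miss both. In that last case nothing is gained.

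**Precision, rough guide.** The 95% CI half-width for a standardised between-arm difference is 1.96 × √(2/(n/2)). This gives 0.51 SD with 60 participants, 0.60 with 42, 0.73 with 29 and 0.80 with 24.

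**Precision at 3 months, simulated.** Assumptions: 30 per arm, correlation 0.6, 15% missing at 8 weeks and 30% at 3 months, independent of each other. Complete cases average 0.85 × 0.70 × 60 = 35.7, and participants with any follow-up (1 − 0.15 × 0.30) × 60 = 57.3. The SD of the 3-month effect estimate is:

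- complete cases, change score: 0.299
- complete cases, baseline-adjusted: 0.273
- all available 3-month data, baseline-adjusted: 0.249
- no use of baseline at all: about 0.31

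In variance terms the full gain is 0.299² − 0.249² = 0.027, of which 0.299² − 0.273² = 0.015, about half, comes from baseline adjustment and not from the recovered records. If dropout is monotone at the same rates (nobody returns), about 42 are complete against 51 with any follow-up. Everyone seen at 3 months is then already a complete case, so recovered records add nothing to this comparison at 3 months; the gain is at 8 weeks.

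**Bias, simulated under an assumed mechanism.** Zero true effect; about 33% of the intervention arm leave after poor 8-week scores; nobody leaves the control arm; equal correlations between visits, from 0.7 to 0.5. The complete-case 8-week change contrast is biased by 0.07 to 0.12 SD when the dropout probability rises gradually with the score (logistic, 0.8 per SD), and by 0.16 to 0.27 SD under a sharp cut-off. Dropout of intermediate strength gave 0.11 to 0.18 SD. The 3-month change contrast was not biased in any of these runs.

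**The case against.** The strongest reply is that the article never states listwise deletion, that fitting detail is normally left to an analysis plan, and that the ANOVA is secondary. The primary endpoints are the Table 3 criteria, progression rests on them, the analysis focuses on descriptive statistics, and missing data and withdrawal reasons will be reported, so any loss would be visible.

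Most of this stands and limits the weight of the point. It does not remove it. The article itself names the model and the missing-data rule, and in their ordinary meaning the two together exclude partial records, next to a claim of intention-to-treat.

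A reader might infer that about half the sample will be lost. The documents do not support that. The 70% and 40% figures are thresholds for a pass, not expected rates, and 29 of 60 is reached only at the floor with independent missingness. A reader might also infer that the analysis will flatter the intervention. That requires poor responders to leave the intervention arm in particular, and nothing in the documents says so. If participants who have recovered leave, or if dropout is mainly in the control arm, the bias can run the other way.

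**Conclusion.** The inconsistency holds: the named analysis cannot honour the stated principle once any follow-up visit is missed, and Table 3 allows for missed visits. Its size is conditional. At the 70% floor, 24 to 42 of 60 would be complete cases; with better completion the loss shrinks. The 8-week bias of roughly 0.1 to 0.2 SD depends wholly on an assumed dropout that is related to the 8-week score and differs by arm. The absence of bias in the 3-month change contrast was likewise shown only under that mechanism with equal correlations.

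The feasibility endpoints and descriptive summaries are unaffected. What is affected is the exploratory effect estimates and the effect sizes and correlations passed on to the full trial. That makes it a moderate issue, worth correcting because the correction is cheap, and not one that undermines the trial's primary purpose.

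**What to change.** Replace the split-plot ANOVA with a linear mixed model for repeated measures, fitted by REML to all available data from every randomised participant, analysed as randomised. Specify visit, arm and arm-by-visit terms with an unstructured covariance. Include baseline explicitly, either as a covariate or as a response constrained to be equal across arms; without it the 3-month SD of about 0.31 is no better than the complete-case change score. Report the adjusted difference with its 95% CI at each follow-up, and the number contributing by arm and visit. The no-imputation rule can stay, since the model is valid under missing-at-random without it.

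If the ANOVA is kept, label it a complete-case analysis, report its n by arm, and do not attach the intention-to-treat label to it.

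The cost is one paragraph of wording and standard software, with no extra data or participants. The downside is a slightly more complex model in a small sample, so use a small-sample degrees-of-freedom correction.

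### The exploratory split-plot ANOVA treats baseline as an outcome level, names neither randomisation stratum, and does not say which term supplies the effect size for the full RCT

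*Protocol article*

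**What the plan says.** The Quantitative data section of the protocol article explores the DASS, PERMA and HRV hypotheses with a "split-plot ANOVA with group (intervention vs control) as a between-subjects factor", "across time (pre vs two follow-up assessments), a within-subject factor". No other factor or covariate is named. Results are to be given with "two-sided tests and 95% confidence intervals where appropriate". The same section says that effect-size estimates and intraclass correlations will feed the sample size of a full-scale RCT. It does not say whether the effect size is the group main effect, the group-by-time interaction or a contrast at a given follow-up.

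The Design and Randomisation sections stratify the 1:1 allocation by site and antidepressant use, the latter "aiming for an equivalent number of participants prescribed antidepressants per site, per arm".

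The Analysis section makes the feasibility criteria in Table 3 the primary endpoints, and Quantitative data states that effectiveness is not assessed definitively.

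**The concern.** Baseline was measured before allocation, so the expected arm difference at that visit is zero. Entered as a third outcome level, it can act on the treatment effect in two ways. In the group main effect it is averaged with the follow-ups. In the group-by-time term it is subtracted at full weight, as a raw change, whatever its correlation with follow-up. Neither use is as precise as taking baseline as a covariate.

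The trial also balances the arms on two factors and then names a model without them. Where those factors are prognostic, the standard error of a between-subject term comes out too large.

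What is at stake is the quality of the estimates handed to the RCT, from at most 60 people. The omnibus interaction has (2 − 1)(3 − 1) = 2 degrees of freedom and is not itself a mean difference at either follow-up, so the article leaves open which number goes forward.

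**Working it through.** **Plan's own figure.** The Abstract says "A total of 60 participants at three sites will be recruited including 20 participants at each site", and Randomisation says "aiming for 10 participants per site, per arm". 3 sites × 2 arms × 10 = 60, or 30 per arm, which agrees. There is no power statement to reproduce, since "Sample size was determined based on our clinical experience running similar interventions".

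**Assumptions.** The article gives no SD, correlation or effect. Take SD 1 at each visit, the same correlation ρ between any two visits, an effect δ equal at both follow-ups, and n per arm.

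**One follow-up.** Variance of the arm difference:
- change score: (2/n) × 2(1 − ρ)
- baseline as covariate: (2/n) × (1 − ρ²)
- ratio: (1 − ρ²) / [2(1 − ρ)] = (1 + ρ)/2 = 0.75, 0.80 and 0.85 at ρ = 0.5, 0.6 and 0.7, a saving of 25%, 20% and 15%.

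**Three visits together.**
- Group main effect: expectation (0 + δ + δ)/3 = 2δ/3; variance (2/n)(1 + 2ρ)/3.
- Group-by-time contrast (mean follow-up minus baseline): expectation δ; variance (2/n)(3/2)(1 − ρ).
- Mean follow-up adjusted for baseline: expectation δ; variance (2/n)(1 − ρ)(1 + 2ρ)/2.

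The contrast therefore has 3/(1 + 2ρ) times the adjusted variance: 1.50 at ρ = 0.5 and 1.25 at ρ = 0.7.

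With n = 30 and δ = 0.5 SD:

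| Term | Expected | SE at ρ = 0.3 | 0.5 | 0.7 | 0.8 |
|---|---|---|---|---|---|
| Group main effect | 0.33 | 0.189 | 0.211 | 0.231 | 0.240 |
| Group-by-time contrast | 0.50 | 0.265 | 0.224 | 0.173 | 0.141 |
| Baseline-adjusted | 0.50 | 0.193 | 0.183 | 0.155 | 0.132 |

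At ρ = 0.5 these correspond to two-sided 5% power of 35%, 61% and 78%. The trial is not powered for efficacy, so this only shows how much information each term uses. Simulation (4,000 trials per scenario, balanced strata) gave mean estimates of 0.33 to 0.34 for the main effect and 0.50 to 0.51 for the other two.

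**Strata.** If the strata explain a share R² of the variance of the between-subject quantity analysed, omitting them inflates its model SE by 1/√(1 − R²): 1.026 at 0.05, 1.054 at 0.10 and 1.118 at 0.20. That is about 3% to 12%. Stratum effects that are constant over time cancel in the group-by-time contrast. Once baseline is a covariate (ρ = 0.5), the simulated model SE without strata is 0.183. Adding them gives 0.178 at R² = 0.10 (0.183/0.178 = 1.03) and 0.172 at R² = 0.20 (0.183/0.172 = 1.06). The two gains therefore overlap and should not be added.

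**The case against.** A reader might infer that the plan reports a treatment effect shrunk by a third. If such an effect were set against an unchanged SD (80% power, two-sided 5%), a true 0.5 SD would be planned as 0.33, giving 142 per arm instead of 63. The article does not support that inference. Its hypotheses concern change over time, which in a split-plot design points to the group-by-time interaction, and that term is undiluted. The shrinkage is one branch of an unspecified choice.

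A reader might also infer that leaving out the strata biases the result, or that the plan passes a residual variance to the RCT. With balanced strata there is no bias; the error is towards wider intervals, and only for between-subject terms. The article mentions effect sizes and intraclass correlations as inputs to the RCT, not a residual variance.

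It is fair to add that this is a condensed article and that covariates are often left to an analysis plan. Not naming the strata is therefore weaker evidence than making baseline a time level, which is stated outright. By-group summaries and confidence intervals are also promised, so differences at each visit could be obtained. Finally, progression rests on the feasibility criteria, and this ANOVA decides none of them.

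What remains is that a particular model has been named, it uses baseline inefficiently whichever term is read, and the term that informs the RCT is not identified.

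**Conclusion.** The point holds as one of efficiency and specification in an exploratory analysis. The main loss comes from the handling of baseline. Its direction is certain for any correlation below 1; its size depends on the assumed correlation, and the three-visit results also on equal correlations and a constant effect at both follow-ups. The two-thirds shrinkage is conditional on using the group main effect. The strata are a secondary matter of precision. The change is worth making because the estimates are meant to guide a larger trial, but nothing here threatens the feasibility conclusions.

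**What to change.** For each exploratory outcome, model the immediate (post-8-week) and 3-month scores with arm, visit and arm-by-visit terms, allowing for correlation between a person's two scores. Adjust for that outcome's baseline score, site and antidepressant use. Report the adjusted arm difference with its 95% CI at each follow-up, and state that this is the effect estimate that informs the RCT. Alongside it, give the unadjusted SD and the baseline-to-follow-up correlation, so that the RCT can be planned under either an adjusted or an unadjusted analysis.

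The cost is about four degrees of freedom (baseline 1, site 2, antidepressant use 1) and a change of wording. Table 2 already schedules the baseline measures, and both strata are known at randomisation, so no new data are needed. The analysis stays exploratory and the Table 3 endpoints are unaffected.
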